### Interventions

#### Therapeutic regimen repaglinide

Therapy started with 3 × 0.5 mg Repaglinide before the main meals. If one meal has been skipped or consisted only of carbohydrate-free food, tablet intake was not recommended. Therapy adjustment (dose increase to 3 × 1 mg or dose reduction to 3 × 0.25 mg) occurred basing on blood glucose level measured 2 hours after a meal. The target value should have been 70–160 mg/dl. If the majority of values were above 160 mg/dl, the dose should have been further increased but not earlier than one week after start of therapy. The maximum dose in this study should have been 12 mg (3 × 4 mg). If low blood glucose levels (hypoglycaemia symptoms or blood glucose level below 50 mg/dl) occurred postprandial or before the next main meal, the repaglinide dose should have been reduced (see Figure 1). Asymptomatic blood glucose levels between 50 and 60 mg/dl could have been tolerated. For some patients, different doses before breakfast, lunch and dinner could have been reasonable.

**Figure 1 F1:**
[figure not shown]
Algorithm for dose adjustment of repaglinide.

During the adjustment phase up to 6 measurements of blood glucose levels were recommended (pre-and postprandial after the main meals respectively). After a stable adjustment was achieved, this number might be reduced for every patient individually, but one postprandial measuring of blood glucose levels had to be maintained daily. Each postprandial blood glucose level had to be checked at least once a week.

Reasons for choosing repaglinide as oral anti-diabetic.

A decreased insulin secretion appeared to be part of CF-diabetes pathogenesis repeatedly. Biguanides, sensitizers and glycosidase inhibitors are only of restricted use with CF patients due to the chemicals’ hepatic or gastrointestinal side effects. In Germany, the most extensive experience with oral anti-diabetics in CF-associated diabetes mellitus therapy has been with glibenclamide [7]. Because of its longer lasting effect the risk of hypoglycaemia, especially when meals are skipped, is higher compared to repaglinide. The latter can be adapted to meals more conveniently. For these reasons glimepiride was not chosen for this study. Nateglinide is a substance whose effects profile is similar to that of repaglinide. This substance was still under approval at the date designing this trial while therapy using repaglinide had already been documented extensively. Therefore, nateglinide was not chosen.

There are individual reports of successful use of repaglinide during CF diabetes [8]; this substance is also used in the USA in a study of adult CF patients with diabetes mellitus (Principal investigator: [name], MD, Minneapolis) [9].

### Therapeutic regimen insulin

Insulin therapy should have been conducted by three injections of Regular Insulin, each time immediately before the main meals. With asymptomatic patients, therapy should begin with 0.05 units per kg weight and injection. The dose was adjusted with regard to postprandial (2 hours after meal) glucose levels: The dose should be adjusted by about 10–20%, approximated to full or half units (see Figure 2). Patients injected insulin using insulin pens.

**Figure 2 F2:**
[figure not shown]
Algorithm for insulin adjustment.

During the adjustment phase, up to 6 blood glucose measurements were recommended (each pre- and postprandial). After a stable metabolism adjustment was attained, this number could have been reduced individually; however, every postprandial level had to be checked once a week. 3 daily measurements were the minimum, especially when using higher insulin doses (>0.3 units/kg and day). Patients with varying blood glucose levels should have been educated about blood glucose corrections based on body weight and insulin demand. If the absorbable carbohydrate content of meals changed significantly on a daily basis, then a separate carbohydrate exchange unit factor for every meal based on pre- and postprandial measurements had to be determined.

### Reason for the choice of insulin therapy scheme

For insulin therapy of CF patients, conventional schemes (1–2 injections a day, fixed or varying mixtures of regular- and NPH-insulin) are advocated as well as intensified therapy schemes with 3, 4 or more injections and flexible adaptation of insulin doses to the expected food intake and the measured blood glucose level [9]. The study described here aimed at CF patients who have been diagnosed early, thus making an intensified therapy scheme unnecessary. In the case of type 2-therapy, which shows some parallels to CFRD, recent years have shown a development away from doses of premixed insulin with high NPH contents and towards pre-prandial doses of regular insulin [10]. Most CF diabetes patients show very high postprandial blood glucose levels, whereas fasting values and pre-prandial values remained normal for a long time. Therefore, a therapy of 3 regular insulin injections is advisable from a pathophysiological viewpoint. A dose of 3 injections a day for CF patients with an early diagnosis of diabetes mellitus appeared to be a viable compromise between the two aims – to apply a therapy scheme as simple as possible and to optimise a patient’s blood glucose levels at the same time.

### Diabetes education at the onset of therapy

All CF patients with newly diagnosed diabetes mellitus had to be educated intensively about food formulations, effects of food on blood glucose, blood glucose measuring, blood glucose documentation, risk of hypoglycaemia during therapy, treatment of hypoglycaemia, long-term effects of high blood glucose levels, and characteristics of diabetes mellitus with CF. Patients who have been randomised to insulin therapy had to be taught additionally about injecting, storage of insulin and dose adjustment.

### Therapy duration

Patients in both therapy strains hade to be monitored for 2 years; every 3 months, a standardised examination and documentation was intended.

### Reasons for study duration

No relevant short-term changes have been expected among early diagnosed patients, especially concerning weight development and lung function [11]. Evidence of successful diabetes therapy with an oral anti-diabetic stretching over 2 years was planned to show constitute clinically relevant results compared with a shorter duration.

### Discontinuation criteria

The therapy in one of the therapy strains should have been considered ineffective if one of the following discontinuation criteria had been met: No acceptable metabolic control obtainable over a time span of 3 months regardless of dose adjustment according to protocol and therapy compliance; occurrence of non-tolerable undesired side effects under therapy; transaminase increase to 3 times the initial value; non tolerable allergic reactions; discontinuation of study by patient/family; se of systemic steroids necessary; desired or occurring pregnancy; PEG/nasal tube feeding/completely parental alimentation of at least 4 successive weeks or transplantation.

### Therapy alternatives when reaching discontinuation criterion

a. Insufficient metabolism control during therapy with repaglinide.

Generally, a shift to insulin would have been necessary; doses of 3 injections of regular insulin before meals were recommended. If fasting blood glucose levels had been high, an additional dose of intermediate/long-lasting insulin before going to sleep was advisable. A shift from repaglinide to glibenclamide would have make sense only if allergic reactions to repaglinide occurred. The use of other oral anti-diabetics could not be recommended based on current scientific knowledge.

b. Insufficient metabolic/glycaemic control during therapy with three injections of regular insulin.

Usually a standard intensified therapy of 4–5 injections a day was recommended.

### Outcome measures

Primary endpoint:

Primary endpoint was the change in HbA1c after 24 months of treatment.

Secondary endpoints:

Secondary endpoints were glycaemic control assessed by mean HbA1C and mean blood glucose profile; change in BMI-Z-score; change in FEV1% predicted and safety assessed by antibiotic therapy, incidence of adverse events, number of hypoglycaemic episodes, all symptomatic hypoglycaemia, hypoglycaemia that necessitates the help of other persons, hypoglycaemia with unconsciousness or coma and number of blood glucose levels below 50 mg/dl in relation to all blood glucose measurements.

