**Methods/Design:**

In all cystic fibrosis patients with an age of 10 years or older, an oral glucose tolerance test is recommended. The result of this test is classified according to the WHO cut off values. It is required to have two diabetes positive oral glucose tolerance tests for the diagnosis of diabetes mellitus.

This study is a multi-national, multicentre, open labelled, randomized and prospective controlled parallel group’s trial, with 24 months treatment.

The primary objective of this trial is to compare the glycaemic control of oral therapy with Repaglinide with insulin injections in patients with cystic fibrosis related diabetes after 2 years of treatment.

The trial should include 74 subjects showing cystic fibrosis related diabetes newly diagnosed by oral glucose tolerance test during annual screening for cystic fibrosis related diabetes.

Patients are randomised by central fax randomisation.

Primary endpoint is mean HbA1c after 24 months of treatment. Secondary endpoints are change in FEV1% predicted and change in BMI-Z-score.

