### Primary objective

The primary objective of this trial is to compare the glycaemic control on oral therapy with repaglinide tid with that on insulin therapy with three daily injections of regular Insulin over 2 years in patients with CF and CFRD.

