### Power calculation/analysis

Which number of patients was necessary to show a significant difference between therapy strains of 80% power on the one hand and p <0.05 on the other? Retrospective HbA1c data from a database of the CF centre at Medical School Hannover were used. Measurements of n = 132 HbA1c within the first two years after diabetes diagnosis of n = 44 patients older than 10 years at the date of diagnosis resulted in an average value of HbA1c = 5.6 ± 1.5 (average value ± SD). Within a similar group (older than 10 years) but without diabetes n = 763 measurements yielded an HbA1c of 4.6 ± 0.68 (average value ± SD). A difference of 1 (which is in the range of individual variations during treatment especially in youngsters and young adults) between therapy groups was considered relevant [12]. Calculation with *n Query®* of necessary patients for each group was done with these parameters: Two group *t*-test of equal means (equal n’s) 1; Test significance level, α 0,050; 2 sided test; Group 1 mean, μ_1_ 5,600; Group 2 mean, μ_2_ 4,760; Difference in means, μ_1_ - μ_2_ 1,000; Common standard deviation, σ 1,500; Effect size, δ = |μ_1_ - μ_2_|/σ 0,667; Power 80%. Based on the above assumptions the number of patients in each group was calculated as n = 37. Over a treatment time of 2 years, about 30% of patients were assumed to drop out of the study. Therefore, n = 111 patients have been necessary at the beginning of the study to ensure a number of n = 74 remaining patients at the end of the study.

For analysis, the differences of primary parameter HbA1c repeated measures-ANOVA will be applied. The one-sided zero hypothesis (Repaglinide is not worse than insulin) will be dismissed if a p value under 0.05 occurs. The two therapy groups will be compared concerning secondary parameters statistically using the fisher exact test (comparison of discrete events), the Wilcoxon (non-parametrically distributed parameters) and the *t*-test (parametrically distributed parameters). For comparison of drop-outs between the treatment stains a Cox proportional-hazard-ratio model will be applied.

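### The primary endpoint is HbA1c level in one place and HbA1c change in another, and neither the sample size nor the repeated-measures ANOVA settles which month-24 contrast is primary

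*Protocol article*

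**What the plan says.** **Endpoint.** The abstract (Methods/Design) says: "Primary endpoint is mean HbA1c after 24 months of treatment". The section Outcome measures says: "Primary endpoint was the change in HbA1c after 24 months of treatment". The same section continues: "Secondary endpoints were glycaemic control assessed by mean HbA1C and mean blood glucose profile". The variable that is primary in the abstract is therefore secondary in the body, where it carries no time point.

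**Objective.** The abstract compares glycaemic control "in patients with cystic fibrosis related diabetes after 2 years of treatment". The section Primary objective compares repaglinide with "three daily injections of regular Insulin over 2 years in patients with CF and CFRD".

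**Sample size** (Power calculation/analysis). A two-sided, two-group t-test at α 0.05 with 80% power, a difference of 1.0 and SD 1.5 gives 37 per group. The SD comes from 132 HbA1c levels in 44 patients within two years of diagnosis. No time point is attached to the difference. The only link to month 24 is that the 74 patients are those remaining at the end of the study.

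**Analysis** (same section). "For analysis, the differences of primary parameter HbA1c repeated measures-ANOVA will be applied". Then: "The one-sided zero hypothesis (Repaglinide is not worse than insulin) will be dismissed if a p value under 0.05 occurs". No visits, model effect or month-24 contrast are named. Table 1 has HbA1c at V1 to V9, that is, every three months from month 0 to month 24.

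**The concern.** A trial needs one stated primary quantity. Here two sections give different ones, and this is a contradiction rather than a detail lost in condensing the protocol to an article.

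The sections that could have settled it do not. The sample size uses an SD of levels, which is not the SD of a change. The analysis is a method with several possible test results. With all quarterly visits entered, a repeated-measures ANOVA gives a group effect, which is a difference averaged over visits, and a group-by-time effect, which is a multi-degree-of-freedom test for any non-parallel course, without direction. Neither is the difference at month 24.

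The trial is open-label, and the section Trial status says the analysis is ongoing. If level, change and visit average all remain available, the choice among them can be made with knowledge of the results, and they can lead to different conclusions.

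**Working it through.** **1. The plan's own figure.** Inputs from Power calculation/analysis: difference 1.0, SD 1.5, two-sided α 0.05, 37 per group. Noncentrality = 1.0 / (1.5 × √(2/37)) = 2.87 on 72 df, critical t = 1.99. Power is 80.8% at 37 per group and 79.7% at 36, so 37 reproduces. It is the size for one HbA1c value per patient with SD 1.5.

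**2. The same 37 per group applied to a change score.** With equal SDs at baseline and month 24, SD(change) = 1.5 × √(2(1 − ρ)), where ρ is the baseline-to-month-24 correlation. The document does not give ρ, so a range is assumed.

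| ρ (assumed) | SD of change | Power at 37 per group | n per group for 80%, change | n per group for 80%, baseline-adjusted level |
|---|---|---|---|---|
| 0 | 2.12 | 52% | 72 | 37 |
| 0.3 | 1.77 | 67% | 51 | 34 |
| 0.5 | 1.50 | 81% | 37 | 28 |
| 0.7 | 1.16 | 95% | 23 | 20 |

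The last column uses residual SD = 1.5 × √(1 − ρ²). Level and change need the same number only at ρ = 0.5. The baseline-adjusted comparison never needs more than 37.

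**3. The ANOVA group effect if all eight post-baseline visits (V2 to V9) enter.** Under compound symmetry with visit correlation r (assumed 0.5 to 0.7), the SD of a patient's visit average is 1.5 × √((1 + 7r)/8): 1.125 at r = 0.5 and 1.288 at r = 0.7. Power is two-sided, α 0.05, 37 per group.

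| Course of the true difference (assumed) | Average over V2–V9 | Power, r = 0.5 to 0.7 |
|---|---|---|
| 1.0 from month 3 on | 1.00 | 96% to 91% |
| Linear growth to 1.0 at month 24 | 0.56 | 56% to 46% |
| 1.0 at month 24 only | 0.125 | 8% to 7% |
| 1.0 at months 3–21, zero at month 24 | 0.875 | 91% to 82% |

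The linear average is (3 + 6 + … + 24)/(8 × 24) = 108/192 = 0.5625. In the last row the test is usually significant although there is no difference at month 24.

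**4. The group-by-time effect over nine visits.** It has 8 numerator df. For the last course above, its noncentrality is (37/2) × 1.556 / (2.25 × (1 − r)), that is 25.6 at r = 0.5 and 42.6 at r = 0.7, and power is 97% to over 99%. Significance therefore does not establish a month-24 difference or its direction.

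**5. The ANOVA if only baseline and month 24 enter.** Group-by-time then has one df and equals a t-test on change scores, which is the endpoint in Outcome measures. The plan does not say that this is intended.

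**The case against.** The strongest reply is that the endpoint conflict is one of wording. Under randomisation, level at month 24 and change to month 24 have the same expected group difference, and once baseline is adjusted for, the treatment estimate is identical. This is correct, and it is why baseline adjustment resolves the conflict. Unadjusted, however, the two differ in precision (step 2) and in their response to chance baseline imbalance, and the plan states no adjustment.

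A second reply is that model details usually belong in the SAP, and that the visit average is nowhere called primary. The absence of detail alone would indeed be no finding. It counts here because the analysis sentence is the one place that could have decided between two conflicting endpoints.

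Third, the power figures rest on assumed correlations and courses, and these run both ways: a change score gains power above ρ = 0.5, and a constant difference gives the visit average more than the planned 80%. This also stands.

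A reader might infer more than the text supports:

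- That the ANOVA cannot test the month-24 difference. No effect is named, and the two-time-point version would test the change.
- That it cannot carry a one-sided hypothesis. A one-df group effect can; only the multi-df test cannot.
- That the trial was expressly sized for month 24. No time point is stated.
- That late loss of control is the reason given for two years of treatment. Reasons for study duration does not mention it. It speaks of slow changes in weight and lung function and of the clinical relevance of two-year success.

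**Conclusion.** The contradiction on the primary endpoint stands on the text alone and needs no assumption. The sizing and the ANOVA do not resolve it.

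Its size depends on quantities that the document does not give. The stated 80% power carries over to a change score only for ρ of about 0.5 or more. If all visits enter the ANOVA, the power of its group effect for a month-24 difference of 1.0 runs from 96% down to 7% with the course of the difference and r between 0.5 and 0.7. These figures assume equal SDs of 1.5, compound symmetry and 37 analysed per group. They show that the choice of endpoint and effect matters. They do not show that the trial is underpowered, nor that the ANOVA is bound to miss the month-24 difference.

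**What to change.** State one primary endpoint in the abstract, the objective, the outcome section and the analysis: the between-group difference in HbA1c at month 24, adjusted for baseline HbA1c. Name that single contrast, with its confidence interval, as the primary result. One suitable model is a mixed model for repeated measures on V2 to V9 with baseline HbA1c, treatment, visit, treatment-by-visit and the stratification factors gender and age group. An unstructured covariance for eight visits has 8 × 9/2 = 36 parameters, which is many for about 74 completers, so a fallback structure should be named in advance. Reconcile the sidedness of the test and interval with the one-sided hypothesis in Power calculation/analysis. Report the month-12 contrast and the visit average as secondary.

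**Cost.** No new data are needed, since HbA1c is in Table 1 at V1 to V9. The sample-size text must be restated as referring to month-24 HbA1c; with baseline adjustment the required number is at most the planned 37 per group.

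**Timing.** Data management describes the database as closed and Trial status says the analysis is ongoing, so this cannot be presented as a routine edit before database lock. Date the decision and make it before comparative results are seen. If they have been seen, disclose it as a later change.

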### Secondary objectives

The secondary objectives of this trial are to compare the two treatment regimen (oral therapy with Repaglinide and insulin therapy with regular insulin) in terms of efficacy and safety.

The efficacy objectives are change in glycaemic control after 12 months of treatment, glycaemic control assessed by glucose profile done monthly (6 values), change in nutritional status and pulmonary function at 12 and 24 months, as well as the need for antibiotic treatments.

The safety objectives are the incidence and quality (mild, severe, other) of hypoglycaemic episodes and adverse events.

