### Randomization

After detailed information by the physicians of the local CF centre, the patient or legal guardian decided to give written informed consent to participate in the study. The trial was open-labelled in order to avoid use of double-dummy technique which would have required an unacceptable increase in the number of injections for the patients. The patients were allocated to the treatment regimen according to a randomisation list generated by a geigy random number table by central fax randomisation. Stratification was conducted according to gender and two age groups (10–15 years, >15 years). Every randomised patient should have been observed for at least 2 years and be included in the final analysis (“intention-to-treat” analysis).

The trial procedures are summarised in the following Table 1.

**Table 1 T1:** Trial procedures

**Visits/months**	**VS**	**V1**	**V2**	**V3**	**V4**	**V5**	**V6**	**V7**	**V8**	**V9**	**End**
		**0**	**3**	**6**	**9**	**12**	**15**	**18**	**21**	**24**	
Informed consent	+										
Selection/exclusion criteria	+										
Randomisation		+									
Inclusion/exclusion criteria		+									
Demographic data	+										
Medical history	+										
Physical examination	+	+	+	+	+	+	+	+	+	+	+
Concomitant illness and medication	+	+	+	+	+	+	+	+	+	+	+
Blood glucose profile			+	+	+	+	+	+	+	+	+
HbA_1c_		+	+	+	+	+	+	+	+	+	+
Pulmonary function		+	+	+	+	+	+	+	+	+	+
IV therapy (antibiotics)		+	+	+	+	+	+	+	+	+	+
Adverse events		+	+	+	+	+	+	+	+	+	+
Hypoglycaemic episodes			+	+	+	+	+	+	+	+	+
Drug dispensation		+	+	+	+	+	+	+	+		

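### Hypoglycaemia, adverse-event and antibiotic endpoints have no observation-time basis, so unequal drop-out would favour the arm that patients leave earlier

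*Protocol article*

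**What the plan says.** All references are to the protocol article.

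- **Secondary objectives:** "The safety objectives are the incidence and quality (mild, severe, other) of hypoglycaemic episodes and adverse events". No time unit is given.
- **Outcome measures:** "safety assessed by antibiotic therapy, incidence of adverse events, number of hypoglycaemic episodes", followed by symptomatic episodes, episodes needing another person's help, and episodes with loss of consciousness or coma. Hypoglycaemic episodes are a number, adverse events an incidence without a unit, and antibiotic therapy has no metric. The list ends with one endpoint that does have a denominator: "number of blood glucose levels below 50 mg/dl in relation to all blood glucose measurements".
- **Power calculation/analysis, tests:** secondary parameters are compared "using the fisher exact test (comparison of discrete events), the Wilcoxon (non-parametrically distributed parameters") and the t-test.
- **Power calculation/analysis, drop-out:** "Over a treatment time of 2 years, about 30% of patients were assumed to drop out of the study". For comparing drop-out between arms, "a Cox proportional-hazard-ratio model will be applied". That model is named for drop-out only.
- **Randomization:** "Every randomised patient should have been observed for at least 2 years and be included in the final analysis", under intention-to-treat.

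**The concern.** A patient seen for 3 months has less opportunity for an episode, an adverse event or an antibiotic course than one seen for 24 months. Fisher's test on patients with and without an event cannot take this into account. Neither can a Wilcoxon or t-test run on totals. If patients leave one arm earlier than the other, that arm accumulates fewer events for this reason alone.

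The comparison at stake is whether repaglinide or insulin causes more hypoglycaemia, which is a stated safety objective. Unequal observation is plausible, though not shown. The trial is open-label and compares tablets with three daily injections. The Discontinuation criteria include poor metabolic control, side effects that cannot be tolerated, and withdrawal by the patient or family, and each of these could differ between arms.

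**Working it through.** **Inputs.** From the document: 2 years of planned observation, about 30% drop-out overall, and 111 patients at entry (taken as 56 and 55). The document gives no event rate, no drop-out by arm and no timing of drop-out, so these are assumptions shown as ranges. It also gives no figure for the safety comparisons that could be reproduced.

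**Step 1: simple illustration.** Let r be the true rate per year, equal in both arms, and d the proportion who leave, each seen for 1 year. Completers are seen for 2 years.

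- Expected episodes per patient = r × [2(1 − d) + d]
- P(at least one) = (1 − d)(1 − e^(−2r)) + d(1 − e^(−r))

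With r = 1, 1 − e^(−2) = 0.8647 and 1 − e^(−1) = 0.6321.

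- d = 0.40: 2(0.60) + 0.40 = 1.60 episodes; P = 0.60 × 0.8647 + 0.40 × 0.6321 = 0.772
- d = 0.20: 2(0.80) + 0.20 = 1.80 episodes; P = 0.80 × 0.8647 + 0.20 × 0.6321 = 0.818
- Ratio of counts 1.60/1.80 = 0.89, and 77% vs 82% with any episode
- d = 0.45 vs 0.15: 1.55 vs 1.85 episodes, ratio 0.84, and 76% vs 83% with any episode

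The true rate ratio is 1.00 in every case.

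**Step 2: drop-out spread over the two years.** With a constant drop-out hazard λ = −ln(1 − d)/2, mean observed time is d/λ. The ratio of mean observed times is also the spurious ratio of mean counts when true rates are equal. P(at least one observed event) = r/(r + λ) × (1 − e^(−2(r + λ))), shown at r = 0.5.

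| Drop-out (higher vs lower) | Mean years observed | Ratio | Any event, r = 0.5 |
|---|---|---|---|
| 30% vs 30% | 1.68 vs 1.68 | 1.00 | 54.7% vs 54.7% |
| 35% vs 25% | 1.63 vs 1.74 | 0.94 | 53.2% vs 56.2% |
| 40% vs 20% | 1.57 vs 1.79 | 0.87 | 51.6% vs 57.7% |
| 50% vs 10% | 1.44 vs 1.90 | 0.76 | 48.2% vs 60.5% |

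**Step 3: effect on the tests.** 1,500 simulated trials per setting, 56 vs 55 patients, equal true rates, two-sided 5% level. Rates were 0.5 and 2 per year without overdispersion, and 2 and 6 per year with it. The table gives the range of false-positive rates.

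| Drop-out | Fisher, yes/no | Wilcoxon, counts | Wilcoxon, per-patient rates |
|---|---|---|---|
| 30% vs 30% | 3–4% | 4–5% | 4–5% |
| 40% vs 20% | 6–14% | 11–20% | 5–6% |
| 50% vs 10% | 16–48% | 27–62% | 6–12% |

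Equal drop-out leaves the tests at their level. Under unequal drop-out the excess rejections favour the arm with more drop-out. Using per-patient rates removes most of the distortion, but not all of it in the extreme case. The negative binomial and Poisson models were not simulated. Their target, events per patient-year, has an expected ratio of 1.00 under these assumptions.

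**The case against.** The strongest reply is that much of this is unstated rather than stated wrongly, and that an article may leave exposure adjustment to a full protocol or analysis plan that is not shown. A reader might infer that the plan commits every one of these endpoints to raw counts or yes/no events. The text does not support that: incidence can mean a rate, antibiotic therapy has no metric, Wilcoxon and t-tests can be run on per-patient rates, and one glucose endpoint already has a denominator. All of this stands. What remains is narrower. Hypoglycaemic episodes are defined as a number, and Fisher's test, which cannot use follow-up time, is the test named for discrete events. That is a stated choice, not just missing detail.

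Second, every randomised patient is meant to be observed for 2 years. A reader might infer that the arm with more treatment failures must look safer. That does not follow, because patients who stop the assigned therapy should remain under observation, and this reduces the bias. It does not remove it, because the sample-size text expects about 30% to leave the study itself.

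Third, the by-arm splits are invented. The planned Cox comparison of drop-out does not show that imbalance is expected, although it would help to reveal one. Drop-out may also depend on events, since side effects are a reason for stopping, and the calculation assumes that it does not. Both objections stand.

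Fourth, the yes/no gap at 40% vs 20% is about 5 percentage points. That is less than one standard error of the difference with about 55 patients per arm: √[(0.77 × 0.23 + 0.82 × 0.18)/55] ≈ 0.077. A single trial could easily mask or exaggerate such a gap. The shift is systematic all the same, and the false-positive rates above show its effect.

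**Conclusion.** The concern holds in a conditional form. The plan gives no observation-time basis for hypoglycaemic episodes, their severity classes, adverse events or antibiotic therapy. It names tests that are not tied to time at risk, and it expects about 30% of patients to leave the study. If observation time differs between arms, the comparison favours the arm left earlier. Under the assumed equal rates, the spurious count ratio is 0.94 to 0.87 for 10- to 20-point differences in drop-out spread over time (0.89 at 20 points if leavers are seen for 12 months), and 0.76 for a 40-point difference.

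The document does not show that the arms will differ, or which arm would benefit; with equal drop-out there is no average bias. The sizes rest on assumed event rates, assumed drop-out by arm, and drop-out unrelated to event risk. These are secondary endpoints, so the primary HbA1c result is unaffected. The specification should still be corrected, because a better method is available at little cost.

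**What to change.** In Outcome measures, define hypoglycaemic episodes (each listed class), adverse events and antibiotic courses per patient-year of observation. In Power calculation/analysis, compare arms with a negative binomial model, or a Poisson model if the counts are not overdispersed, with log observation time as offset. For rare severe events, replace Fisher's test with time to first event. Report observation time by arm next to the safety results. The glucose endpoint can keep its present denominator.

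**Cost.** The rate analysis needs only event counts and observation time, so it is mainly a change of wording. Time to first event needs more: Table 1 shows that adverse events, hypoglycaemic episodes and IV antibiotics are recorded at visits, but does not say that event dates are. If they are not recorded, use the visit interval in which the first event was reported. The rate model assumes a constant rate over the two years, and both methods assume that drop-out is not driven by event risk. Trial status says the analysis is already under way, so the change should be dated and declared, with the named tests kept as supplementary results.
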